**Summary**

| **Overall project title:** | Remote Cognitive Behavioural Therapy for LGBTQ+ People with Anxiety Disorders: An Exploratory Trial |
| --- | --- |
| **Protocol version** | 2.3 |
| **Objectives** | **Primary**  The primary objective of this program of research is to understand how efficacious cognitive behavioural therapy (CBT) is when delivered via videoconferencing for anxiety disorders in LGBTQ+ adults.  **Secondary**  The secondary objectives of this project are: 1) to benchmark the efficacy of adapted CBT compared to standard CBT for LGBTQ+ adults, when both are delivered via video-conferencing; 2) to understand the feasibility of delivering CBT to LGBTQ+ adults via video-conferencing; and 3) understand the perspectives of LGBTQ+ participants on the content, delivery format, and acceptability of CBT delivered via telehealth for anxiety disorders. |
| **Study design** | A randomized controlled trial (RCT) compliant with CONSORT-R guidelines, comparing an immediate treatment group with a waitlist control group, with a nested qualitative study to examine acceptability of the treatment. |
| **Planned sample size** | A total sample of 52 participants, with 26 participants in each group. Qualitative interviews will use 8 - 10 participants from each intervention group, with a total of 16 - 20 included participants in qualitative evaluation interviews. |
| **Selection criteria** | RCT Inclusion criteria: (1) Residing in Australia currently; (2) aged 18 years or over; (3) Fluent in English; (4) Meets criteria for an anxiety disorder as the primary diagnosis and the disorder is of at least ‘moderate severity’ (defined as a score of 4 on the DIAMOND module severity measure); (5) On a stable dose of psychotropic medication or medication free; (6) Not receiving regular psychological services currently for their anxiety symptoms (defined as sessions at least once a week with a qualified mental health professional); (7) Identify as LGBTQ+, and; (8) Has access to a private location with internet to complete the treatment for the duration of the study.  RCT Exclusion criteria: (1) Suicide risk as assessed by item 9 of the PHQ-9 (a score of 2 or above) at baseline, a score of ‘moderate’ or higher on the C-SSRS, responses of ‘yes’ on item 1-3 on the risk questionnaire, or via clinician judgement during the diagnostic interview; (2) Daily use of alcohol or illicit drugs (meaning illegal drugs, pharmaceutical drugs used outside of their prescribed or intended use, and other substances inappropriately used); (3) The presence of a schizophrenia spectrum disorder as assessed by the DIAMOND semi-structured clinical interview; (4) Any significant cognitive/intellectual impairment as assessed during the diagnostic interview; (5) A medical condition that may interfere with treatment; (6) No access to a computer with a camera and stable internet on a regular basis; (7) Is not willing to engage in treatment on a regular basis using internet-videoconferencing software; (8) Does not identify as non-heterosexual or non-cisgendered; (9) Does not indicate any anxiety disorder symptoms on the DIAMOND Self Report screener. |

| **Statistical considerations** | **Sample size calculation**  The sample size calculator developed by Faul et al. (2007) was used to calculate a total sample size of 52 participants, in samples of 26 for each group, to detect a large effect (*d* = .80) with 80% power. Previous research has indicated that CBT has a large effect size for anxiety disorders (Cuijpers et al., 2013). To detect clinically significant differences in participant diagnostic status, 42 participants will need to be recruited, in samples of 21 in each group, using the ClinCalc LLC (2024) sample size calculation tool.  A total of 16 – 20 participants will be selected for inclusion to the qualitative study, with eight to ten participants each from each intervention group. Braun and Clarke (2013) recommend that 10 to 20 participants are typically sufficient to identify themes, although, previous researchers have suggested that fewer participants may be needed if the sample holds more information power. This sample size is consistent with other sample sizes in this area of research (Jackson et al., 2022; Pachankis et al., 2020). Participants will be selected based on a representative matrix to achieve a maximally diverse qualitative sample, consistent with other qualitative studies (Christensen et al., 2023).  **Analysis plan**  To ensure analyses manage missing data conservatively, intent-to-treat principles and mixed-linear models will be used for quantitative analyses. Mixed-models are used to analyse longitudinal clinical trial data robustly. Using an appropriate covariance structure and maximum likelihood estimation will provide unbiased estimates in the event of missing data, assuming that data is missing at random. Qualitative data will be analysed using framework analysis (Ritchie & Spencer, 1994). |
| **Study duration** | 5 years |

**BACKGROUND**

Internationally, approximately 18 - 37% of adults will develop an anxiety, mood, or related disorder in their lifetime (McGrath et al., 2023). These disorders are known as internalising disorders because of their tendency to turn inwards in response to stressors, which results in high levels of anxiety, distress, and negative affect (Krueger, 1999). These are differentiated from externalising disorders, which have a tendency to respond to with stressors with outward coping mechanisms such as excessive use of alcohol and other substances. Depressive disorders can include conditions such as major depressive disorder and persistent depressive disorder, and anxiety disorders often include conditions such as generalised anxiety disorder, panic disorder, and social anxiety disorder. These disorders have significant impacts on people’s functioning (Vigo et al., 2016) and quality of life (Hohls et al., 2021), and represent a large burden on people’s lives (Greenberg et al., 2021; Konnopka & König, 2020).

In Australia, while the general population’s 12-month prevalence rate of internalising disorders is high at 8 – 17%, it is two to three times higher among lesbian, gay, bisexual, and other non-heterosexual people at approximately 28% to 50% (Australian Bureau of Statistics, 2023). Similarly, approximately one in three gender-diverse people were reported to have experienced an internalising disorder in the past 12 months (Australian Bureau of Statistics, 2023). This higher rate of internalising disorders in LGBTQ+ people is not due to any inherent psychopathology: rather, the higher rate of stigma and discrimination experienced by these groups is proposed to account for these disparities (Hatzenbuehler, 2009; Meyer, 2003). The excess stress of dealing with chronically high levels of stigma and discrimination is called minority stress (Meyer, 2003). While structural and social-level change is needed to reduce minority stress in LGBTQ+ people, implementing this change can take significant time (Hinshaw & Stier, 2008) and may be incomplete in addressing the issue effectively (Kalev et al., 2006). Thus, tailored treatments for LGBTQ+ unique minority stressors and common internalising disorders are needed to support a reduction in symptoms and quality of life in LGBTQ+ people (Barrera & Castro, 2006).

Cognitive behaviour therapy (CBT) is recommended as the gold-standard, first-line treatment for internalising disorders (American Psychological Association Presidential Task Force on Evidence-Based Practice, 2006; Australian Psychological Society, 2018; National Institute for Health and Care Excellence, 2011). CBT’s effectiveness has been shown across 106 meta-analyses, with a medium to large effect size for treating any internalising disorder (Hofmann et al., 2012). Comorbidity between internalising disorders is high (Kessler et al., 2011), and treatments have been developed to address multiple internalising disorders simultaneously. This is known as transdiagnostic treatment. The Unified Protocol (Ellard et al., 2010) is a well-researched type of transdiagnostic treatment that has been demonstrated to have large effect sizes for internalising disorders in the general population (Sakiris & Berle, 2019). Additionally, preliminary controlled trials have shown that an LGBTQ-adapted Unified Protocol for LGBTQ+ adults is also effective at reducing symptoms of internalising disorders (Ellard et al., 2010; Pachankis et al., 2015; Pachankis et al., 2020b). In two randomised control trials of LGBTQ+ adapted CBT, Pachankis et al. (2015) and Pachankis et al. (2020) found comparable effect sizes pre- to post-treatment for anxiety and related disorders and depressive symptoms as in trials of the Unified Protocol in the general population. It is important to understand if LGBTQ-adapted CBT is more effective than standard CBT, but to date, no clinical trials have directly compared the two treatments or measured standard CBT’s efficacy in LGBTQ+ people. This study will contribute to the emerging evidence of equivalence between the two treatments by understanding the preliminary efficacy of both interventions, and assessing feasibility to progress to a larger trial where both treatments are directly compared.

Similarly, few studies have used telehealth-delivered CBT for internalising disorders in LGBTQ+ adults (Van Der-Pol Harney & McAloon, 2018). Despite this, remotely delivered CBT has demonstrated effectiveness for internalising disorders (Matsumoto et al., 2021). LGBTQ+ people face logistical barriers that may prevent them from seeking care, including exclusion from healthcare from non-affirming/non-educated providers or a desire to conceal their ‘outness’ by accessing affirming care (Foy et al., 2019; Olfson et al., 2000). Remotely delivered CBT provides a solution to mitigate these barriers for LGBTQ+ people but is yet to be explored in the literature.

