**OBJECTIVES, DESIGN, AND HYPOTHESES**

The purpose of this study is to examine the efficacy, feasibility, and acceptability of videoconferencing-delivered CBT for anxiety disorders in LGBTQ+ adults. A CONSORT-R compliant, two-group, randomised control feasibility trial (RCT) will examine the research questions. The hypotheses for this study are below:

1. Videoconferencing-delivered, standard CBT will result in significant reductions in symptoms with a large between-group and within-group effect size at post-treatment and three-month follow-up.
2. Videoconferencing-delivered, LGBTQ-adapted CBT will result in a similar degree of symptom reduction when compared to standard CBT.
3. Videoconferencing-delivered standard CBT and LGBTQ-adapted CBT will be feasible to deliver to LGBTQ+ adults with diagnosed anxiety, as assessed by at least 80% treatment fidelity (Borrelli et al., 2005), at least 80% retention following the waitlist period (Fernandez et al., 2015).
4. Videoconferencing-delivered CBT will be acceptable to LGBTQ+ adults with diagnosed anxiety disorders, as assessed in qualitative semi-structured exit interviews and by at least 70% treatment retention and questionnaire completion at follow-up (Fernandez et al., 2015).

The study’s design has two groups:

**Group 1 (*n* = 26): Immediate treatment group.** Group 1 will immediately receive standard, unadapted CBT delivered via videoconferencing. This treatment will be delivered via Zoom. Participants in Group 1 will receive one 50-minute session per week for eight weeks.

**Group 2 (*n* = 26) Waitlist control group.** Group 2 will commence the treatment after a waitlist period of nine weeks, and will recomplete screening measures and their diagnostic interview. Group 2 will receive a similar CBT treatment delivered via Zoom, but this treatment has been tailored to account for the unique challenges experienced by LGBTQ+ people (Pachankis, 2014). LGBTQ-adapted treatment has been shown to be efficacious in previous trials (Pachankis et al., 2015; Pachankis et al., 2020).

A waitlist control was chosen given no studies have currently investigated standard CBT for internalising disorders in LGBTQ+ individuals. As such this study is designed as a feasibility study, phase 1 clinical trial.

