**PARTICIPANT NUMBERS & POWER**

Using G*Power, it was determined that 52 participants would be needed to detect a large, post-treatment, between-group effect size with alpha set to 0.05 and 80% power (Faul et al., 2007). This is because previous meta-analyses have detected large effect sizes for the effect of CBT on anxiety (Cuijpers et al., 2013). Previous preliminary randomised control trials of CBT for LGBTQ+ adults with both internalising and externalising disorders have recruited samples of similar sizes (Pachankis et al., 2015; Pachankis et al., 2020).

Power was also calculated to detect clinically meaningful changes in participant anxiety disorder diagnosis according to DSM criteria. Using the ClinCalc LLC (2024) sample size calculation tool, the recruitment of 42 participants would be sufficient to detect a post-treatment between-group clinically meaningful change in anxiety disorder diagnosis with 80% power and alpha set to 0.05. This is based on the anticipated incidence of anxiety remission drawn from the metanalysis of Springer et al. (2018), which found that 55.8% of anxiety disorder diagnoses remitted after receiving CBT. For waitlist controls, anxiety disorder symptoms in participants in waitlist control fell below the clinical cut-score 15.4% of the time (Scott et al., 2022). Given CBT has not been examined in trials of LGBTQ+ participants with only internalising disorders (Van Der Pol-Harney & McAloon, 2018), an exact power analysis is unable to be determined and is thus an exploratory estimate. However, 95% confidence intervals will be reported with any effect estimates to determine the intervention's precision.

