**Figure 1.**

*Study Flow Diagram*

Pre-screened for eligibility.

Participants who do not meet criteria will be excluded.

Allocated to waitlist control condition with LGBTQ-Affirmative Unified Protocol after 9-week waitlist period ends (n = 26).

Diagnostic status and self-report measures re-administered prior to treatment.

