**ANALYSIS PLAN**

To meet the study’s aim (i.e., to understand if the treatment is efficacious for reducing symptoms of anxiety disorders ), the following analyses will be conducted. The main analyses looking at treatment outcomes from the RCT will be carried out using conservative intention-to-treat principles and using mixed-linear models analyses to handle missing data. Mixed-models are a robust statistical approach for analysing longitudinal clinical trial data and these analyses will employ an appropriate covariance structure and maximum likelihood estimation, which provides unbiased estimates in the case of missing data, under the assumption that data is missing at random. These analyses account for the effect of missing data, thus additional participant recruitment to account for drop-out rates is not warranted. Using this dataset, other appropriate analyses arising from secondary papers will also be conducted. Participants have been informed in the PICF that other secondary data analyses will be conducted on the data that they provide during their participation in the research trial. This may include intersectional moderator analyses of treatment efficacy based on person-level stigma moderators from the minority stress model to inform further treatment adaption needs (Barrera & Castro, 2006; Meyer, 2003). Comparisons between the standard treatment and the LGBTQ-affirmative CBT protocol will be compared using benchmarking analyses (Minami et al., 2008).

To understand the treatment’s efficacy, clinically significant change will be measured using three methods. Diagnostic change will be assessed from pre- to post-treatment and at follow-up using the DIAMOND structured interview. Treatment response will be measured using the reliable change index (RCI) of Jacobson and Truax (1991) to understand which change on the OASIS is not attributable to measurement error, but rather is statistically reliable. Any increase in symptoms by the RCI magnitude of change will be defined as deterioration in this trial. Clinically significant change at post-treatment and to follow-up will be defined as a score below the cut score of 8 on the OASIS (Campbell-Sills et al., 2009).

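### Adapted CBT has no concurrent untreated comparator, so the Background's claims of preliminary efficacy for both treatments and of evidence towards equivalence exceed the design

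*Protocol*

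**What the plan says.** The Background states: "This study will contribute to the emerging evidence of equivalence between the two treatments by understanding the preliminary efficacy of both interventions". The same sentence goes on to feasibility and leaves direct comparison to a larger trial; the means it names are, in full, "understanding the preliminary efficacy of both interventions, and assessing feasibility to progress to a larger trial where both treatments are directly compared". In Objectives, Design, and Hypotheses, the second hypothesis is that "LGBTQ-adapted CBT will result in a similar degree of symptom reduction when compared to standard CBT".

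The Summary gives two arms: "A total sample of 52 participants, with 26 participants in each group". Adapted CBT is given only to the control arm: "Group 2 will commence the treatment after a waitlist period of nine weeks". In Table 1, Group 2 has a Baseline at Week 0, a second pre-treatment assessment at Week 9 and a post-treatment assessment at Week 18. Group 1 has its post-treatment assessment at Week 9.

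The Analysis Plan measures efficacy in three ways. The first is diagnosis: "Diagnostic change will be assessed from pre- to post-treatment and at follow-up using the DIAMOND structured interview". The second is reliable change on the OASIS. The third is an OASIS score below 8 at post-treatment and follow-up. Standard and adapted CBT are to be compared by benchmarking.

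The section on participant numbers and power gives an untreated rate: "anxiety disorder symptoms in participants in waitlist control fell below the clinical cut-score 15.4% of the time".

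**The concern.** Randomisation creates one controlled contrast, immediate standard CBT against waitlist at Week 9. Once Group 2 starts adapted CBT, Group 1 has finished its own treatment, so nobody is untreated in Weeks 9 to 18. A pre-to-post change in Group 2 then mixes the effect of adapted CBT with natural recovery, regression to the mean and outside care, which the Treatment section says control participants may use. The Analysis Plan names nothing that separates these for adapted CBT.

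The re-assessment at Week 9 removes wait-period improvement from change scores. It does not do so for the cut-score endpoint, which is a status after treatment with no requirement to have scored 8 or more at Week 9. A participant who drops below 8 while waiting and stays there counts as an adapted-CBT success.

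At stake is what the trial may say about adapted CBT. An uncontrolled change reported as efficacy, and then set beside standard CBT as evidence of equivalence, would be read as more than it is.

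**Working it through.** **1. The protocol's own figures.** A two-sided, two-sample t-test with d = 0.80, alpha 0.05 and 80% power needs 25.52, so 26 per group (power 0.807), which gives the stated 52. Comparing 55.8% with 15.4% without continuity correction needs 21 per group (power 0.803), which gives the stated 42. Sidedness is not stated; two-sided reproduces both. Both calculations concern immediate standard CBT against waitlist. Neither covers the adapted-CBT phase.

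**2. Who is untreated, by period (Table 1 timing).**

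| Period | Group 1 | Group 2 | Untreated group running? |
|---|---|---|---|
| Weeks 0 to 9 | standard CBT | waiting | yes, Group 2 |
| Weeks 9 to 18 | treatment finished | adapted CBT | no |

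The wait is eight weeks in the Summary's study procedures and in parts of the Treatment section, and nine elsewhere. These passages must be reconciled, but the table's last column is the same either way.

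**3. Size on the cut-score endpoint.** Inputs: 26 in Group 2 and the 15.4% waitlist rate.

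26 × 0.154 = 4.0 participants.

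This is the most that wait-period improvers would add if all of them stayed below 8 to Week 18. It assumes that the cited cut-score rate carries over to the OASIS cut of 8. For new untreated improvement within Weeks 9 to 18 the protocol gives no rate. Change soon after selection is likely to be larger than later change, so 15.4% may be too high for that window.

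For scale, against the protocol's 55.8% remission figure: 55.8 − 15.4 = 40.4 points, and 15.4 / 55.8 = 28%. This share is only approximate, because one rate is for a cut-score and the other for diagnosis.

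**4. Continuous outcome.** Suppose adapted CBT had no effect and untreated change in Weeks 9 to 18 had a paired standardised size d_z (assumed). The chance of a significant pre-to-post improvement at n = 26, against a nominal 0.025 in that direction, would be:

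| d_z | 0.1 | 0.2 | 0.3 | 0.4 | 0.5 |
|---|---|---|---|---|---|
| probability | 0.07 | 0.16 | 0.31 | 0.50 | 0.69 |

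**5. What the scheduled data can offer.** Group 2 has the OASIS at Weeks 0, 9 and 18. With Y for the score, the wait-adjusted contrast is

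(Y18 − Y9) − (Y9 − Y0) = Y18 − 2·Y9 + Y0.

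In SD units, with correlation r between adjacent assessments:
- raw change: variance 2(1 − r)
- contrast, compound symmetry: 6 − 8r + 2r = 6 − 6r
- contrast, AR(1): 6 − 8r + 2r²

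The 95% half-width is 1.96 × √(variance / 26). At r = 0.6 the variances are 0.80, 2.40 and 1.92.

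| assumed r | raw change | contrast, AR(1) | contrast, compound symmetry |
|---|---|---|---|
| 0.5 | 0.38 | 0.61 | 0.67 |
| 0.6 | 0.34 | 0.53 | 0.60 |
| 0.7 | 0.30 | 0.45 | 0.52 |

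With the dropout rates cited under Participant Retention, 26 × (1 − 0.159) × (1 − 0.264) ≈ 16 would complete. At r = 0.6 the half-width among completers is then 1.96 × √(1.92/16) = 0.68 to 1.96 × √(2.40/16) = 0.76 SD.

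**The case against.** The best defence is that the protocol already keeps most of its controlled claims to standard CBT. Hypothesis 1 reserves the between-group effect for standard CBT. Hypothesis 2 asks only for a similar reduction, and the Summary makes adapted CBT a secondary, benchmarked objective. The protocol chose the waitlist because standard CBT is the untested treatment in this population, and cites earlier controlled trials for adapted CBT. The Background says preliminary and defers direct comparison. An extra secondary contrast is also something a statistical analysis plan might carry.

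Much of this stands, and it narrows the point. It does not rescue the Background sentence: preliminary speaks to precision, not to missing control, and equivalence still goes beyond two uncontrolled changes with different starting points relative to enrolment. That mismatch lies in the protocol itself.

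Several stronger readings are tempting and not supported:

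- **Adapted CBT has no comparator at all.** Standard CBT is a planned benchmark. It is non-concurrent and gives no untreated reference, but it is a comparator.
- **The adapted-CBT efficacy result decides progression.** The Background ties progression to feasibility. The numerical criteria are retention (80% and 70%), recruitment (52 or 42) and fidelity (80%), with questionnaire completion also assessed. None is an efficacy threshold for adapted CBT.
- **The bias in Weeks 9 to 18 is 15 percentage points.** The 15.4% is a general waitlist rate, and no figure is given for this later window. Upward bias is the expected direction, not a certainty.
- **The raw change is an upper bound.** It exceeds the adjusted estimate only if Group 2 improves while waiting. If Group 2 worsens, even by chance, the order reverses.

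Outside care is recorded by the Service Use Questionnaire, but no adjustment for it is described.

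**Conclusion.** The point holds as one of claim and labelling. The trial can estimate a controlled effect of standard CBT at Week 9. For adapted CBT it can report an uncontrolled pre-to-post change and a non-concurrent benchmark. Neither supports a claim of efficacy in its own right or a contribution to evidence of equivalence.

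The size that can be put on it from the protocol is at most about 4 of 26 wait-period improvers counted as successes on the cut-score endpoint. That rests on the 15.4% rate applying to the OASIS cut of 8 and on all of them staying below it. The contribution of untreated change in Weeks 9 to 18 is unknown and may be smaller. The half-widths rest on assumed correlations and 26 complete cases. The primary comparison and the sample-size calculations are not affected.

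**What to change.** **Wording.** In the Background, confine controlled efficacy to standard CBT versus waitlist at Week 9, describe the adapted-CBT result as an uncontrolled pre-post change, and remove the claim that it contributes evidence of equivalence. Make the same distinction where the Summary objectives and the opening of Objectives, Design, and Hypotheses speak of the efficacy of CBT in general.

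**Analysis Plan.** Add, as a secondary sensitivity estimate, the OASIS contrast within Group 2 of (Week 18 minus Week 9) minus (Week 9 minus Week 0), with a 95% confidence interval, reported beside the raw change. Report Group 2's status against the cut of 8 at Week 9 alongside Week 18, so that those already below it are visible. State that the contrast may over-correct, because the wait period directly follows selection, and that it is imprecise, more so with dropout. Do not call the raw change an upper bound.

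**Cost.** A protocol wording change, one contrast and one extra tabulation, all from assessments already scheduled. No added participants, visits or measures. The price is a weaker stated claim for adapted CBT and a wider interval for the adjusted estimate.
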